### Data management

The data will be collected daily by the investigators. For the intra-operative data (respiratory and cardiovascular components, bleeding, and need for catecholamines or aerosols), they will be collected prospectively and transmitted by the anesthesiologist following each procedure. The exposure will be evaluated just after the procedure by the “operator” surgeon. The visual analogic scale at 2, 4, 8, and 24 h as well as the time before gas, stool, sitting, and walking are reported prospectively on a document that follows the patient at each time. The total amount of analgesics will be calculated on the day of discharge. All information required by the protocol will be recorded on the patient’s study notebook and a second time on electronic notebooks, and an explanation will be provided for each missing data variable. The entry will be made in FileMaker 9.0 version 3 (database software) stored on the network of Bordeaux University Hospital, which guarantees the confidentiality and security of the data processing in accordance with the requirements of the CNIL Reference Methodology. In accordance with the legislation in force, persons having direct access to the source data will take all the necessary precautions to ensure the confidentiality of the data. During or at the end of the research, the data collected on the individuals who are suitable for this analysis will be anonymized prior. The Bordeaux University Hospital network benefits from a daily backup of its data. The database is also stored and archived under the responsibility of the investigator in the colorectal surgery department of the Haut-Leveque Hospital of the Bordeaux University Hospital. For database freezing, a version number and a date will be given to the database, which is kept in a format that no longer allows modifications. A freeze certificate of the database will be completed and sent to the sponsor (EN-RCL-601). Data transfers (sending and receiving) will be carried out in accordance with the CMG procedure. For security reasons, the data files are anonymized and transferred via the secure platform CIRRUS.

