### Intervention

The “operator” surgeon is the surgeon who performs the procedure. The team is made up of six different surgeons, each with their own patients and using the same surgical techniques. The “evaluator” surgeon is the surgeon who validates the patient’s discharge according to predefined and objective criteria. The operating surgeon does not validate the discharge of his own patients. The patient also ignores the arm in which he or she was randomly assigned. The results of randomization are known only by the department’s clinical researchers and kept in a password-protected Excel database. The result is communicated only to the “operator” surgeon on the day of the operation. He knows the randomization arm because it is up to him to adjust the insufflation pressure during the procedure. On day 0, the “operator” surgeon performs a laparoscopic colectomy by using the AirSeal® medical device (ConMed, Utica, NY, USA) and adjusts the insufflation pressure in accordance with the results of the randomization: low-pressure insufflation at 7 mm Hg or standard-pressure insufflation at 12 mm Hg. Different anesthesia and analgesia may affect the secondary outcomes, post-operative pain scores, consumption of analgesics, and recovery time. This is why the anesthetic and analgesic protocol are standardized in both groups and explained in schematic form in the Appendix. The intra-operative protocol starts before the introduction of the trocar: we infiltrate the orifices with 2% naropeine. Then the patient receives a continuous infusion of ultiva, ketamine (0.3 mg/kg as a loading dose and then 0.15 mg/kg per hour until the end of the surgery), and xylocaine (continuous dose of 1.0 mg/kg, stopped 1 h before the end of the surgery). One hour before the end of the surgery, we perform a morphine bolus of 0.1 mg/kg, 50 mg of profenid, and 1000 mg of paracetamol. In the post-operative care room, a morphine titration will be performed if necessary (the amount of morphine given is notified) and the patient receives 1000 mg of paracetamol again 1 h after the surgery is completed. In the post-operative period, the patient systematically receives 1000 mg of paracetamol every 6 h and 50 mg of profenid every 6 h for 48 h. The patient also receives 50 mg of topalgic only if needed and all doses are notified (maximum 8 per 24 h). Perioperative respiratory and cardiovascular management are also standardized. Cardiovascular data will include systolic blood pressure, diastolic blood pressure, mean arterial pressure, heart rate, cardiac index, stroke volume, and stroke volume variation. We also collect the volume of hydration and filling, balance of inputs and outputs, and total doses of ephedrine and noradrenaline (if needed). Respiratory data will include tidal volume, end-tidal CO_2_, respiratory frequency, peak pressure, peak pressure, plateau pressure, driving pressure, compliance (exhalation pressure at 0 and 8 mm Hg), exhalation volume (at 0 and 8 mm Hg), inspired fraction of O_2_, O_2_ saturation, and functional residual capacity. The aerosols are used only if necessary in case of obstructive pathology (asthma or chronic obstructive pulmonary disease). The aerosol used if necessary is Salbutamol (beta-2 mimetics). The degree of muscle relaxation is monitored throughout the interventions using the TOF (Train of Four): four short stimulations of 0.2-ms duration, spread over 2 s. It measures the ratio between the response of the fourth and first stimulation (T4/T1 ratio) or counts the number of responses (from 0 to 4). We measure the TOF via the response of the ulnar nerve (thumb adduction) by using a device located on each patient’s wrist. For all procedures, the TOF must be equal to 0. The post-operative mobilization of the patient and the gastrointestinal recovery will be carried out in accordance with the ERAS (Enhanced Recovery After Surgery) early rehabilitation protocol [15]. Criteria for discharge will be carried out by a surgeon different from the one who performed the operation (“evaluator surgeon”). The patient will be hospitalized for the post-operative period in the colorectal unit of Magellan Medico-Surgical Centre. The follow-up will be standardized regardless of the randomization arm. All inpatient and outpatient adverse events will be recorded and reported. As part of the standard care in our colorectal unit, all patients have a post-operative consultation at 30 days (+15 days maximum) Fig. 1.

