### Outcomes

The primary outcome is to determine whether low-pressure (7 mm Hg) instead of standard-pressure (12 mm Hg) pneumoperitoneum during laparoscopic colonic resection leads to a reduction of the length of hospital stay of at least 1 day. The theoretical discharge date is the date of medical discharge of the patient, evaluated daily between 7 and 8 a.m., in accordance with predefined criteria, which are no pain requiring the use of analgesics more than stage 2, no nausea or vomiting, no fever of more than 38 °C, resumption of a normal diet, transit (passage of flatus/stool), patient mobilization, and patient acceptance. The real discharge date is the date of discharge including a possible continuation of hospitalization for non-medical reasons (i.e., waiting for convalescent home, personal suitability of the patient).

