Secondary outcomes are to determine how low-pressure pneumoperitoneum (7 mm Hg) influences: patient's post-operative pain (visual analogue scale after 2, 4, 8, and 24 h after surgery), the consumption of level 1, 2, and 3 analgesics, the transit and gas recovery time (days), the time before first time sitting and walking, the evolution of the perioperative cardiovascular and respiratory parameters (arterial blood pressure, heart rate, cardiac output, vascular filling, driving pressure, arterial oxygen saturation [SAO_2_], and post-exercise circulatory occlusion [PECO]), the operating time (from incision to closing, in minutes), the amount of bleeding, the visual quality of the procedure, the laparoscopy conversion rate to normal pressure or laparotomy, ability to achievean R0 resection in cancer surgery, the number of lymph nodes on the specimen and the rate of medical and surgical complications during the first postoperative 30 days (according to the DINDO classification). It seemed important to us to select post-operative pain because it is one of the major factors influencing the patient’s length of stay and very interesting to know whether a lower insufflation pressure makes it possible to reduce pain related to abdominal distention on the one hand and scapular pain on the other hand, which is described as extremely frequent in most laparoscopic procedures. The amount of analgesics (level 1, 2 and 3) is an objective data wich allows us to evaluate pain, wich is a subjective data. In addition, regarding the number of deaths currently associated with chronic opioid use, it seemed that defining whether low pressure allows opioid savings in the post-operative period was a major objective. We also know that taking opioids increases the time before transit resumes and that this influences the length of stay.

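### Analgesic consumption is totalled to discharge, so a shorter stay can lower it with daily need unchanged; it should be tested over fixed windows

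*Protocol article*

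**What the plan says.** Outcomes lists "the consumption of level 1, 2, and 3 analgesics" as a secondary outcome, with no time window and no per-day rate. The pain score beside it has fixed times: "visual analogue scale after 2, 4, 8, and 24 h after surgery". The same section interprets the endpoint: "The amount of analgesics (level 1, 2 and 3) is an objective data wich allows us to evaluate pain". It adds that "defining whether low pressure allows opioid savings in the post-operative period was a major objective".

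The only rule on accumulation is in Data management: "The total amount of analgesics will be calculated on the day of discharge". Statistical analysis compares quantitative secondary criteria by t test or Mann–Whitney test, two-sided at 5%, with no adjustment for length of stay.

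On the drugs, Intervention says that after surgery "the patient systematically receives 1000 mg of paracetamol every 6 h and 50 mg of profenid every 6 h for 48 h". Topalgic 50 mg is given as needed, every dose is recorded, and no end date is stated. Morphine is described only during surgery and in the recovery room, where the titrated amount is recorded.

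The primary endpoint is theoretical length of stay. Sample size assumes 5 ± 2 days in the control arm and a 1-day reduction. The pain criterion for discharge is "no pain requiring the use of analgesics more than stage 2".

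**The concern.** The length of the counting period is itself an outcome, and the one the intervention is meant to change. If low pressure shortens stay, patients in that arm have fewer days in which doses can be counted. Any drug still being taken at discharge will then show a lower total, even if patients need the same amount per day. The discharge criterion allows analgesics up to level 2, so use can continue uncounted at home after an earlier discharge.

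The risk is that one effect is reported twice: once as a shorter stay and again as less pain or less opioid. Pain scores end at 24 h, so they cannot show whether a difference in later consumption reflects pain. Data management also does not say whether theoretical or real discharge closes the total. If it is real discharge, days spent waiting for non-medical reasons also add to it.

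**Working it through.** **Inputs from the document.** Stay 5 days (control) and 4 days (low pressure, from the 1-day target), SD 2; 69 per arm; secondary tests two-sided at 5%; paracetamol 1000 mg every 6 h, that is 4 g/day.

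**Assumptions, since the document gives no use pattern.** SD 2 in both arms, identical daily need in both arms, and the topalgic rates, their decline and the between-patient variation used below.

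**1. The plan's own figure.** n = 2(z₀.₉₅ + z₀.₉₀)²σ²/δ² = 2 × (1.645 + 1.282)² × 4 / 1 = 68.5, so 69 per group. It reproduces. At the two-sided 5% level used for the tests, 1/(2 × √(2/69)) = 2.94 and power is Φ(2.94 − 1.96) = 0.836.

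**2. Constant use to discharge, no variation between patients.** The total is rate × stay, so apparent sparing is 1 − 4/5 = 20%. If scheduled paracetamol runs to discharge, the totals are 4 × 5 = 20 g and 4 × 4 = 16 g, with SD 4 × 2 = 8 g. The standardised difference is 4/8 = 0.5, the same as for stay (1/2), so rejection is again 0.836. Simulation with gamma-distributed stays gave 83% (t) and 87% (Mann–Whitney). Skewed whole-day stays with Mann–Whitney gave 92%.

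**3. Constant as-needed use, 2 topalgic doses/day (assumed).** Means are 10 and 8 doses, again 20% apart.
- Poisson dose counts only: variances are 10 + 4 × 4 = 26 and 8 + 4 × 4 = 24. SE = √(50/69) = 0.851, 2/0.851 = 2.35, and Φ(2.35 − 1.96) = 0.65. Simulation: 64% (t), 69% (Mann–Whitney).
- Need also varying between patients, CV 0.5: variances are 1.25 × 4 × 29 − 100 + 10 = 55 and 1.25 × 4 × 20 − 64 + 8 = 44. SE = √(99/69) = 1.198, 2/1.198 = 1.67, and Φ(1.67 − 1.96) = 0.39. Simulation: 38% (t), 48% (Mann–Whitney).

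**4. Use that declines after surgery.** Assume 4 doses/day at the start and CV 0.5 between patients. Expected doses by day L are 4(1 − e^(−λL))/λ, with λ = ln 2 / half-life. Simulated results:

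| Half-life | Mean total, 5 vs 4 days | Apparent sparing | Rejection (t) |
|---|---|---|---|
| 2 days | 452 vs 403 mg | 11% | 18% |
| 1 day | 271 vs 254 mg | 6% | 8% |
| 0.5 day | 143 vs 141 mg | 1.5% | 5.5% |

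**5. Paracetamol limited to 48 h.** Mean totals were 7.95 and 7.72 g, about 3% apart. The tests still rejected in 62% (t) to 68% (Mann–Whitney) of trials, because a fixed-schedule total varies only through patients who leave before 48 h. That frequency depends on how many do so: with skewed whole-day stays, only about 2% of stays were under 2 days. On either reading of the schedule, the level 1 total says little about pain.

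**6. Alternatives, same data as step 3 with CV 0.5.** A fixed 24-h total and a per-day rate each gave no difference in means and 4.7% rejection (t). A 48-h total left about 3% difference and 6% rejection, again because of discharges before 48 h.

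**7. No difference in stay.** With a mean of 5 days in both arms, rejection for the totals to discharge was about 5%. The artefact needs a difference in stay.

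**The case against.** The sentence in Data management says when the total is computed; it does not formally define the endpoint. The article is condensed, and a window may stand in a fuller document. That is fair, but the sentence is the only accumulation rule given, and the article pairs it with a stated interpretation and an unadjusted test. The point concerns that combination, not a missing detail.

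Three stronger readings are tempting, and the document does not support them.

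- A reader might infer that a false finding of sparing is almost certain once stay is shorter. The 92% figure needs constant daily use, no variation between patients, skewed stays and a Mann–Whitney test. Statistical analysis expects a roughly Gaussian primary variable and a t test. Post-operative need would be expected to fall, and step 4 shows how far that shrinks the effect. For paracetamol the figure also needs dosing to discharge, and it cannot apply to profenid, whose 48-h limit is explicit.
- A reader might infer that the trial cannot address opioid sparing at all. Recovery-room morphine is recorded separately and hardly depends on stay. The exposure is mainly through topalgic.
- A reader might infer that any reduction would be pure artefact. Outcomes treats pain and opioid use as influences on stay, so part of a difference could be real. The total to discharge cannot separate the two.

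In-hospital consumption is also a legitimate descriptive quantity, so there is no case for removing it.

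**Conclusion.** The point holds as a should-fix. The stated total closes at the primary outcome, and nothing in the document offsets that. At the design effect (5 vs 4 days, SD 2, 69 per arm) with identical daily need, apparent sparing of drugs that may be taken to discharge runs from about 1.5% to 20%. The chance of a significant difference runs from about 5%, when use is concentrated in the first day, to about 80–90%, when use is constant to discharge and does not vary between patients. For as-needed topalgic at a constant 2 doses/day with CV 0.5, it is 38–48%.

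These figures rest on assumed use patterns and on stay really differing by 1 day. The primary endpoint and the sample size are not affected. The severity comes from the interpretation: the protocol calls opioid saving a major objective, and the distortion favours the experimental arm if that arm has the shorter stay.

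**What to change.** Before the database is frozen:

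- Define analgesic consumption by level over fixed windows from end of surgery, 0–24 h and 0–48 h, and test those. State how patients discharged before 48 h are handled in the second window.
- Use recovery-room morphine plus as-needed topalgic, in one opioid-equivalent unit, as the opioid-sparing measure.
- Report scheduled level 1 drugs descriptively, not as evidence on pain.
- Keep the total to discharge as descriptive only, optionally with a per-day rate. Say which discharge date closes it, and do not read it as a measure of pain.
- Make clear in Intervention whether the 48-h limit applies to paracetamol as well as profenid, so that the level 1 figures can be interpreted.

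The cost is the redefinition of one secondary endpoint. Recovery-room morphine and every topalgic dose are already recorded, and data are collected daily. The small downside is that use after 48 h is described and not tested.

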### Statistical analysis

The main analysis will focus on all randomly assigned patients (intention-to-treat analysis). The alpha risk is 5% and the power is 90%. Given the main variables studied, there will be no missing data for analysis of the primary outcome. The descriptive statistical analysis will include the following for each quantitative parameter at each time: average, standard deviation, minimum, maximum, median and quartiles, and number of missing values. The categorical variables will be expressed by the frequency of distribution and the associated 95% bilateral confidence intervals. For the primary endpoint, which is theoretical length of hospital stay, the two groups will be compared by using Student’s *t* test if, as suggested by a preliminary study, the distribution of the variable does not deviate significantly from a Gaussian distribution; otherwise, a Mann–Whitney test will be used. For the secondary endpoints, the categorical criteria will be analyzed by using a chi-squared test. In the event that the chi-squared validity criteria are not verified, an exact probability test will be used. Quantitative secondary criteria will be compared by *t* test or Mann–Whitney according to their distribution in the sample considered. All tests will be bilateral at risk of the first species set at 5%. The analysis will be performed by using IBM SPSS Statistics, version 20 software (IBM, Armonk, NY, USA).

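### Analgesic consumption is totalled to discharge, so for drugs that can continue until then a shorter stay lowers the total even when daily need is the same

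*Protocol article*

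**What the plan says.** Only the Data management section of the article says how consumption is added up: "The total amount of analgesics will be calculated on the day of discharge". The Outcomes section lists "the consumption of level 1, 2, and 3 analgesics" as a secondary outcome and gives it no time window, although it fixes the pain scores in the same sentence ("visual analogue scale after 2, 4, 8, and 24 h after surgery").

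Outcomes gives the measure two tasks. It is the objective counterpart to the pain score ("The amount of analgesics (level 1, 2 and 3) is an objective data wich allows us to evaluate pain"), and it serves the opioid question: "defining whether low pressure allows opioid savings in the post-operative period was a major objective".

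Statistical analysis compares quantitative secondary criteria by t test or Mann–Whitney and mentions no adjustment for days in hospital. The same section names the primary endpoint: "For the primary endpoint, which is theoretical length of hospital stay". Sample size plans for a 1-day difference in that stay.

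**The concern.** A total that closes at discharge is counted over each patient's own stay. Stay is a post-randomisation outcome, and it is the one the trial is powered to change. If low pressure shortens stay for any reason, for example earlier transit, that arm contributes fewer days to the sum, and doses taken at home are not counted. Two arms with the same need on each day would then show different totals, always in favour of the shorter-stay arm.

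At stake is the reading of a secondary outcome to which the article gives weight. A lower total could be reported as less pain or as opioid saving when part of it is only fewer counted days.

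Data management also does not say whether its discharge is the theoretical or the real date, both of which Outcomes defines. With the real date, days spent waiting for non-medical reasons add doses as well.

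**Working it through.** **Inputs from the article.** Control stay 5 days with SD 2, difference 1 day, one-sided 5%, power 90%, 69 per arm (Sample size); t test or Mann–Whitney, two-sided (Statistical analysis); drug schedules (Intervention); discharge criteria (Outcomes).

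**Assumed, because the article gives nothing.** The course of daily use over the stay and its coefficient of variation (CV) between patients.

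**Step 1: the planning scenario.** n per arm = 2 × (1.645 + 1.282)² × 2² / 1² = 68.5, so 69 per arm and 138 in total, as stated. A stay of 5 versus 4 days is therefore the scenario the trial is built on.

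**Step 2: which drugs can accrue with stay.**

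| Drug | What the article says | Does the total depend on stay? |
|---|---|---|
| Morphine | Bolus before the end of surgery; titration in the recovery room; no ward use described | No |
| Profenid | Every 6 h, ending at 48 h | No, for stays of at least 2 days |
| Paracetamol | "In the post-operative period, the patient systematically receives 1000 mg of paracetamol every 6 h and 50 mg of profenid every 6 h for 48" (unit: hours). That limit may cover both drugs or only profenid | Unclear |
| Topalgic | As needed, no stated end; the discharge criteria exclude only analgesics above stage 2 | Yes |

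The article does not assign drugs to levels. Topalgic is taken here as the level 2 opioid.

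**Step 3: size by arithmetic.** Let use on day d be r × f^(d−1), the same in both arms. The total over L days is r(1 − f^L)/(1 − f), or rL when f = 1. The relative difference is T(4)/T(5) − 1:

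- constant use (f = 1): 4/5 − 1 = −20%
- use falling 25% a day (f = 0.75): 0.6836/0.7627 − 1 = −10.4%
- use halving daily (f = 0.5): 0.9375/0.96875 − 1 = −3.2%

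If paracetamol does continue every 6 h, a day is 4 × 1000 mg = 4 g. One day less is then 4 g less by schedule alone.

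**Step 4: size by simulation.** Both models use 69 per arm, SD 2, stay rounded with a minimum of 2 days, and identical daily need in both arms. Model A draws stay and patient rate from gamma distributions (3,000 trials, CV 0.3 to 1.0). Model B draws stay from a normal distribution and daily doses from a Poisson distribution with a gamma patient effect of variance 0.25, 0.5 or 1.0, i.e. CV about 0.5 to 1.0 (1,500 trials). The last two columns give two-sided Mann–Whitney rejection at 5%.

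| Use pattern | Total in shorter-stay arm | Model A | Model B |
|---|---|---|---|
| Constant | 18–19% lower | 72%, 50%, 25%, 19% (CV 0.3, 0.5, 0.8, 1.0) | 34%, 24%, 16% |
| Falling 25% a day | about 10% lower | not run | 14%, 11%, 7% |
| Halving daily | 4–5% lower | 6–14% | 6–7% |
| Fixed 0–48 h total | no systematic difference | 4.5–5.3% | 4–6% |

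In Model B the constant-use means are 10.1 and 8.3 doses at 2 doses a day, that is 5.05 and 4.15 days. The 2-day minimum thus trims the gap to 0.9 day, which explains 18% instead of 20%. At CV 0.5 the models differ (50% against 34%); Model B adds dose-count noise and draws stay differently. The rejection rates therefore depend on the model; the direction does not.

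**The case against.** Data management describes when and by whom data are captured, so the quoted sentence may say only when the tally is made. The article is condensed, and a full protocol could hold the window. That lowers certainty about intent. It does not remove the point: a total struck at discharge with no other window given covers the stay, and this is the only aggregation rule stated.

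A reader might infer that the whole opioid-saving objective is confounded with the primary endpoint. The document does not support that. The morphine described is finished by the recovery room, profenid ends at 48 h, Outcomes names the levels separately, and nothing says they are pooled. This part of the objection stands in full.

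It also stands that the size is unknown. The largest figures need use that stays flat to the last day; if use halves daily, the effect is near nominal. With equal stays there is no artefact.

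Finally, consumption in hospital is a real quantity, and the simulations make stay independent of need, whereas Outcomes regards pain and opioids as influences on stay. A lower in-hospital total is then not false. It answers a different question from need at equal time, and need at equal time is what an objective measure of pain requires.

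**Conclusion.** The point holds for as-needed topalgic, and for paracetamol if it continues beyond 48 h. For these, the stated rule lets the primary endpoint set the observation time of a secondary outcome. Under the planned 1-day difference and identical daily need, the total is about 18–20% lower at constant use, about 10% lower if use falls by a quarter each day, and about 3–5% lower if it halves. The use patterns are assumptions.

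A reader might also infer that the plan sets out to explain a shorter stay by a lower analgesic total. The article does not plan that analysis. It says only that the amount helps to evaluate pain and that opioids can delay transit and so affect stay. The risk is one of later interpretation, in a secondary outcome; the primary comparison is not affected.

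**What to change.** In Outcomes and in Data management, define the tested consumption outcome, by analgesic level, over a fixed window from the end of surgery that is the same for every patient, and set it before unblinding. An example is 0–48 h, supported by 0–24 h. Keep the total to discharge as a description only, say whether that discharge is the theoretical or the real date, and do not use it as evidence of less pain. The Intervention section should also make clear which drugs its 48 h limit covers, so that readers can tell which totals depend on stay.

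The cost is about one sentence in the outcome definition. As-needed doses and recovery-room morphine are already recorded, and data are collected daily, so only the summation window changes. Two small downsides remain. Use after the window leaves the tested outcome, and a patient discharged before the window closes needs a stated rule (the simulations assume that nobody leaves before day 2). A single morphine-equivalent sum is optional and not part of this correction.
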